3.5 Termination of study

The study can be stopped if the following conditions occur:

(1) Serious adverse events occurr during the study;

(2) There are serious protocol errors;

(3) Insufficient research funding;

(4) The administrative authorities request that the study is stopped.

3.6 Quality control

(1) Researchers

1) All participants will be trained in the protocol;

2) The investigators will screen the cases strictly according to the inclusion and exclusion criteria;

3) Researchers fill in data carefully and truthfully;

4) In order to minimize bias, all the included patients will be followed uo by the same researcher who is unaware of the grouping.

(2) Subjects

1) When subjects are enrolled, they will be given a detailed introduction to the study protocol by the researcher, especially risks and benefits;

2) Written informed consent will be signed by the subjects or their legal representatives;

3) Participants can withdraw from the study at any time without any reason.

3.7 Statistical analysis

The primary outcome of this study was the quality of recovery score (QoR-15) at 24 h postoperatively. The minimal clinically important difference (MCID) in the QoR-15 scale was 8.0. According to previous research, the sample size calculation showed that 42 subjects in each group were required to achieve 80% power with an α of 0.05. To allow for a dropout rate of 10%, we finally enrolled 46 subjects in each group in this study.

The SPSS21.0 software (IBM) was used for statistical analysis. Shapiro-Wilk test was used to test the normality of the data. Data with normal distribution were presented as mean and standard deviation (SD), and comparisons between groups were analyzed using A Student’s *t*-test. Datas collected at multiple time points were analyzed using repeated measures analysis of variance (ANOVA). Data with non-normal distribution were expressed as median (interquartile range). The Mann-Whitney *U* test was used for intergroup comparisons. The categorical data were shown as numbers (%) and analyzed using the chi-square test or Fisher’s exact test as needed. A two-sided test *P*-value less than 0.05 was considered statistically significant.

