3.4 Outcomes

(1) Primary outcome

The primary outcome of this study is quality of recovery at 24 h after surgery, and it is assessed using the QoR-15 scale. The QoR-15 will be evaluated at three timepoints: before(T_before_), 24h(T_24h_) and 72h(T_72h_) after surgery.

(2) Secondary outcomes

1) The levels of NLRP3, IL-1β and IL-18 will be recorded at T0, T1, T3 and T4;

2) The duration of sugery, consumption of remifentanil, cisatracurium [dosage](javascript:;), application of vasoactive drugs;

3) MAP (mean arterial pressure) and HR will be recorded at before induction (T_0_), after the establishment of carbon dioxide pneumoperitoneum (T_1_), after closing the carbon dioxide pneumoperitoneum (T_2_), and at the end of surgery (T_3_);

4) Rescue analgesia during PACU, respiratory recovery time (the duration of time from withdrawal of anesthetics to return of spontaneous breathing), response time (the duration of time from withdrawal of anesthetics to a verbal command), extubation time (the duration of time from withdrawal of anesthetics to extubation).

5) VAS pain scores at rest (VAS-R) and on coughing (VAS-M) at 4h, 8h, 12h, 24h and 48h postoperatively; times of effective PCIA press at 24h and 48h after operation, the consumption of oxycodone, the use of additional analgesic drugs.

6) Hospital stay durations, intestinal function recovery time (the duration of time from extubation to the first exhaust time), time of first eating or drinking (the duration of time from extubation to the first drinking or eating time), ambulation time (the duration of time from extubation to the first bed time standing or walking), and adverse events such as nausea, vomiting, dizziness, hallucination and nightmare,etc.

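### The primary analysis of 24 h QoR-15 is left to a normality test, with repeated measures ANOVA as a possible third route, and no effect estimate with a confidence interval is named to set against the 8.0-point MCID

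*Protocol*

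**What the plan says.** Protocol section 3.7 names the endpoint: "The primary outcome of this study was the quality of recovery score (QoR-15) at 24 h postoperatively". Beside the sample size it gives one effect size: "The minimal clinically important difference (MCID) in the QoR-15 scale was 8.0". The size itself is given as follows: "According to previous research, the sample size calculation showed that 42 subjects in each group were required". The power is put at 80% and α at 0.05. No SD is stated.

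The analysis rules that follow are generic to continuous data:

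- The gate: "Shapiro-Wilk test was used to test the normality of the data". Its significance level is not given, nor whether it is applied to each arm, to the pooled scores or to residuals.
- If normal: mean and SD, with Student's t-test.
- If not normal: median and interquartile range, with the Mann-Whitney U test.
- Data from several time points: repeated measures ANOVA.

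None of these rules exempts or singles out the primary outcome. Section 3.4 adds, on the same scale: "The QoR-15 will be evaluated at three timepoints" (before surgery, 24 h and 72 h).

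**The concern.** The outcome data themselves choose the primary method, and the candidates do not answer the same question. A t-test concerns a difference in means. Mann-Whitney compares whole distributions, and speaks to a difference in medians only if one arm's distribution is a pure shift of the other's. Repeated measures ANOVA may deliver an effect averaged over time or a group-by-time interaction, and neither is the 24 h contrast.

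The trial will be judged by whether esketamine moves the 24 h score by a clinically important amount. If the rank branch is taken, the planned output is two medians, two interquartile ranges and a P-value. That can show a difference but gives no interval for its size. The t-test branch names no mean difference with interval either, although one follows directly from the two means and SDs.

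**Working it through.** **Inputs.** From section 3.7: 42 per group, power 80%, α 0.05, two-sided, MCID 8.0. From section 3.1: 1:1 allocation. Assumed, because the protocol gives none of them: the SD, the shape of the QoR-15 distribution, the level and unit of the Shapiro-Wilk test, and the correlation between baseline and 24 h scores. That 8.0 is the design difference is an inference; it is the only effect size given.

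**1. The plan's sample size.** Without an SD, the 42 cannot be strictly reproduced. Solving n = 2(1.960 + 0.842)² SD² / 8² for n = 42 gives

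SD = 8 / (2.802 × √(2/42)) = 13.1

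(12.9 with the t distribution). At SD 13, n = 2 × (2.802 × 13/8)² = 41.5, so 42. SD 12 would need 36 per group, SD 14 would need 49 and SD 15 would need 56. The stated size therefore fits a comparison of means with a difference of 8 and an SD of about 13, which is used below.

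**2. How often the gate changes the method.** Simulated trials (4,000 to 6,000 per scenario), 42 per arm. Assumed rule: Shapiro-Wilk P < 0.05 in either arm leads to Mann-Whitney, otherwise the t-test. Skewed scores come from gamma distributions.

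| Assumed distribution | Switch to rank test |
|---|---|
| Normal | about 10% |
| Absolute skewness 0.5 | about 35% |
| Absolute skewness 1.0 | about 84% |
| Absolute skewness 1.6 | nearly 100% |

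The 10% for normal data is what two tests at 5% should give: 1 − 0.95² = 0.0975. If the pooled scores are tested instead, it is about 4%. The unstated unit of testing thus matters too.

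**3. Type I error and power.** The two-step rule's type I error was 4.6% to 5.9% across runs, with simulation error of up to about 0.4 percentage points. Power with a shift of 8 and SD 13:

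| Distribution | t-test | Mann-Whitney | Two-step rule |
|---|---|---|---|
| Normal | about 80% | 78–79% | 79–81% |
| Skewness 1.0 | 79–80% | 84–85% | 84–85% |
| Skewness 1.6 | 79–80% | about 93% | about 93% |

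The t-test keeps roughly its design power of 80% at every shape. Under the two-step rule, power is unchanged or higher.

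**4. What a fixed mean difference would deliver.** At SD 13 the standard error is 13 × √(2/42) = 2.84, so the 95% CI half-width is 1.96 × 2.84 = 5.6 points before baseline adjustment. This is in QoR-15 points and can be read directly against 8.0.

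**5. What baseline adjustment recovers.** With correlation r between baseline and 24 h scores, the residual SD is 13√(1 − r²). Power at 42 per arm for a difference of 8 (t distribution):

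| r | Residual SD | Power |
|---|---|---|
| 0 | 13.0 | 80% |
| 0.3 | 12.4 | 83% |
| 0.4 | 11.9 | 86% |
| 0.5 | 11.3 | 90% |
| 0.6 | 10.4 | 94% |

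Set against step 3, ANCOVA matches the rank test at skewness 1.0 when r is about 0.3 to 0.4. At skewness 1.6 it does so only when r is near 0.6.

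**The case against.** The strongest reply is that nothing invalid happens. The type I error holds and the gate costs no power; with skewed scores it gains some. A reader might infer that choosing the test from the data inflates false positives or weakens the trial. The calculations do not support that.

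A reader might also infer that the rank branch loses the QoR-15 scale altogether. It does not. The medians are in QoR-15 points and can be subtracted and read informally against 8.0. What stands is narrower: no such difference and no interval are planned, and Mann-Whitney does not test a difference in medians without the shift assumption. Because the t-test branch names no estimate either, the gap does not come from the gate alone.

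It can be said that estimates and intervals belong in a statistical analysis plan, which may exist but is not at hand. Silence on them would not be a finding by itself. But the protocol is not silent about the method: it fixes a data-driven rule and applies it to the primary outcome.

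Finally, adding a Hodges-Lehmann shift with CI to the rank branch would close part of the gap without replacing the test. That is fair, but the primary method would still depend on the data, and the repeated measures route would remain open.

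**Conclusion.** The point holds as one of pre-specification and interpretability, not of validity. Section 3.7 lets the data choose between two primary tests and leaves a third analysis arguable. No branch names an effect estimate with an interval to set against 8.0.

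The chance of a switch is about 10% even with normal data and rises to about 84% and nearly 100% at absolute skewness 1.0 and 1.6. These figures assume testing in each arm at 0.05 with 42 per arm. The skewness values are assumptions, since the protocol describes no distribution for QoR-15. The power figures further assume SD 13 and a pure shift of 8 points. The ambiguity of method does not depend on these assumptions; it rests on the text of sections 3.4 and 3.7. It should be corrected, but it does not threaten the design.

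**What to change.** State in section 3.7, before group codes are opened:

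- **Primary analysis:** the difference between groups in mean 24 h QoR-15, adjusted for baseline QoR-15 by ANCOVA, with 95% CI, read against 8.0. It is used whatever the Shapiro-Wilk test shows.
- **Sensitivity analysis:** Mann-Whitney U with a Hodges-Lehmann shift and its CI.
- **Secondary only:** repeated measures models of QoR-15 over time.
- **Normality rule:** limited to the choice of summaries in descriptive tables.

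The change is one of wording. Baseline QoR-15 is already collected under section 3.4, and the sample size stays at 42 per group before dropout.

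The price is possible power. At SD 13 and a shift of 8, an unadjusted mean comparison has about 80%, against about 84% for the rank test at skewness 1.0 and 93% at 1.6. Baseline adjustment makes this up at a correlation of about 0.3 to 0.4 in the first case, but only near 0.6 in the second. The protocol gives no correlation, so under strong skew the loss may not be recovered. The rank sensitivity analysis would keep that information in view.

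### No analysis named in section 3.7 adjusts the 24 h QoR-15 comparison for the preoperative score, so precision already paid for may be lost

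*Protocol*

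**What the plan says.** Protocol section 3.4 makes QoR-15 at 24 h the primary outcome and sets the assessment times: "The QoR-15 will be evaluated at three timepoints: before(T_before_), 24h(T_24h_) and 72h(T_72h_) after surgery". Section 3.7 repeats the endpoint ("The primary outcome of this study was the quality of recovery score (QoR-15) at 24 h postoperatively") and then lists methods by type of data:

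- Normally distributed data: "comparisons between groups were analyzed using A Student" t-test.
- Non-normal data: the Mann-Whitney U "test was used for intergroup comparisons".
- Repeated data: "Datas collected at multiple time points were analyzed using repeated measures analysis of variance (ANOVA").

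The section does not say which of these is the primary test. It names no covariate and no analysis of covariance.

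The sample size statement in the same section gives two facts: "The minimal clinically important difference (MCID) in the QoR-15 scale was 8.0", and "42 subjects in each group were required to achieve 80% power with an α of 0.05". It gives neither an SD nor a correlation between preoperative and 24 h scores.

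**The concern.** A preoperative measurement of the primary outcome is often the most useful covariate a small trial has. Here it is scheduled for every patient, yet no listed method uses it to sharpen the 24 h comparison.

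Under the t-test or Mann-Whitney U, the preoperative score plays no part. Under repeated measures ANOVA it enters as an outcome level. The group main effect then averages the 24 h difference with a preoperative difference whose expected value is zero under randomisation.

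At stake is the width of the confidence interval, and with it the power, in a trial sized at 42 analysable patients per arm. A chance imbalance in preoperative QoR-15 would also carry partly into an unadjusted 24 h difference.

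**Working it through.** **Inputs from section 3.7:** 42 per group, power 80%, two-sided alpha 0.05, and an MCID of 8.0, taken here as the design difference (the text does not expressly call it that). Section 3.1 gives 1:1 allocation.

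**Not in the protocol:** the SD of QoR-15, back-solved below, and the correlation r between preoperative and 24 h scores, taken over 0.1 to 0.7.

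**Step 1. The plan's own figure.** With no SD stated, 42 per group cannot be reproduced independently, but it can be inverted. For a two-sample t-test (noncentral t, 82 df), 80% power at a difference of 8 requires SD = 12.93. The normal formula gives 8 × √(42/2) / (1.960 + 0.842) = 13.09. The sample size is therefore consistent with an unadjusted comparison of two means and an SD of about 13. I use 12.93 below.

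**Step 2. Unadjusted comparison.** SE = 12.93 × √(2/42) = 2.82. The 95% CI half-width is 1.989 × 2.82 = 5.61 points, and power is 80.0%.

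**Step 3. ANCOVA with preoperative QoR-15 as covariate.** Residual SD = 12.93 × √(1 − r²), with 81 df. The last column, 42/(1 − r²), is the number of unadjusted patients per arm that would give the same variance.

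| r | Residual SD | 95% CI half-width | Power | Equivalent n per arm |
|---|---|---|---|---|
| 0 (unadjusted) | 12.93 | 5.61 | 80.0% | 42 |
| 0.1 | 12.87 | 5.59 | 80.4% | 42.4 |
| 0.2 | 12.67 | 5.50 | 81.6% | 43.8 |
| 0.3 | 12.34 | 5.36 | 83.6% | 46.2 |
| 0.5 | 11.20 | 4.86 | 89.9% | 56.0 |
| 0.7 | 9.24 | 4.01 | 97.5% | 82.4 |

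**Step 4. Repeated measures ANOVA, group main effect.** Assume equal SDs and equal correlations at the three times, no expected difference before surgery, 8 points at 24 h and x points at 72 h. The averaged difference is (0 + 8 + x)/3 and the SD of a patient's mean is 12.93 × √((1 + 2r)/3).

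- r = 0.3 (SD 9.44): power is 48% for x = 4 (average 4.00) and 72% for x = 8 (average 5.33).
- r = 0.5 (SD 10.56): power is 40% for x = 4 and 63% for x = 8.

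The 72 h differences are assumptions. In each of these cases the main effect has less power than the plain t-test.

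**Step 5. Chance imbalance.** If the preoperative SD is similar (an assumption), the standard error of the preoperative difference is also about 2.82 points. The expected carry-over into the unadjusted 24 h difference is r times the imbalance. At r = 0.5, a one-standard-error imbalance moves it by about 0.5 × 2.82 = 1.4 points, against an MCID of 8.

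**The case against.** The other side has a good case on several counts.

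- **No test is assigned to the primary outcome.** A reader might infer that the plan ignores the preoperative score, because the t-test rule has no covariate. The protocol does not establish that. The t-test sentence is a general rule for normal data, and the ANOVA sentence, read literally, covers QoR-15 with the preoperative score included. This stands. It does not rescue the plan, because the ANOVA does not use the score as a covariate either.
- **The ANOVA is not only its main effect.** The group-by-time interaction is tested against within-patient error, so the dilution in step 4 does not apply to it. This also stands. But the interaction tests whether the profiles differ over time and does not directly estimate the 24 h difference. Its baseline-to-24 h contrast has variance proportional to 2(1 − r), which improves on the unadjusted 24 h comparison only when r exceeds 0.5 and is never smaller than ANCOVA's 1 − r². Section 3.7 does not say which term would be read.
- **An unadjusted comparison is valid.** Under 1:1 randomisation it is unbiased, keeps its type I error and matches the sample size calculation. This stands in full, so a reader should not infer bias or an invalid test.
- **The gain is not assured.** Both SD and r are absent from the protocol, and at r of 0.1 to 0.2 the gain is under two percentage points of power. Nor does a baseline imbalance pass whole into the result; only about r times its size does.
- **Covariates are often left to a statistical analysis plan.** One may exist. But section 3.7 goes beyond leaving the matter open: it commits to specific tests, none of them adjusted.

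**Conclusion.** The point holds as a matter of efficiency. Preoperative QoR-15 is planned, and no method named in section 3.7 adjusts the 24 h comparison for it. The cost ranges from nearly nothing at r = 0.1 to 0.2, through about ten percentage points of power and 0.75 points of CI half-width (5.61 to 4.86) at r = 0.5, to about 17 percentage points at r = 0.7. If the group main effect of the repeated measures ANOVA became the primary test, power would be about 40% to 72% in the scenarios worked above, against the planned 80%.

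These figures assume a design difference of 8.0, an SD back-solved from the protocol's own sample size, 42 analysable patients per arm, a linear relation between the two scores and, for the ANOVA, the stated 72 h differences and equal correlations. The direction of the benefit is secure for any appreciable correlation; its size is not. Adjustment should be made, but the trial remains interpretable without it.

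**What to change.** In section 3.7, replace the open choice of tests for the primary outcome with wording such as: *The single primary analysis of QoR-15 at 24 h is an ANCOVA with treatment group as factor and preoperative QoR-15 as covariate, reported as the adjusted mean difference with its 95% CI, at a two-sided alpha of 0.05, whatever the result of the Shapiro-Wilk test. The unadjusted t-test or Mann-Whitney U is a sensitivity analysis. Repeated measures ANOVA of QoR-15 is a secondary description of the time course.*

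The last two sentences are needed; without them the competing tests stay open beside the new one.

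The cost is a few lines of text and one degree of freedom, with no new data and no more patients. Section 3.7 is written partly in the past tense, and the document does not settle whether data have been seen. If they have already been unblinded, the change should be reported as made after that point.

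### The blanket repeated-measures ANOVA rule leaves the deciding test for QoR-15 at 24 h open and treats pre-treatment values as outcomes

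*Protocol*

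**What the plan says.** Protocol section 3.7 fixes the endpoint: "The primary outcome of this study was the quality of recovery score (QoR-15) at 24 h postoperatively". It then gives test rules by type of data. For normally distributed data, "comparisons between groups were analyzed using A Student" t-test; for non-normal data, the Mann-Whitney U "test was used for intergroup comparisons". Between these stands a third rule: "Datas collected at multiple time points were analyzed using repeated measures analysis of variance (ANOVA". It names no outcomes, no time points, no ANOVA effect (group, time or interaction) and no contrast.

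Section 3.4 sets the measurement times: "The QoR-15 will be evaluated at three timepoints: before(T_before_), 24h(T_24h_) and 72h(T_72h_) after surgery". For the markers, "The levels of NLRP3, IL-1β and IL-18 will be recorded at T0, T1, T3 and T4". MAP and HR are recorded from T0 to T3. Section 3.3 places T0 before induction and the esketamine loading dose after induction, so T_before and T0 are pre-treatment values. VAS is recorded only after surgery (4 to 48 h), and effective PCIA presses only at 24 h and 48 h after it.

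**The concern.** Two stated rules cover the same primary endpoint. QoR-15 at 24 h is a two-group comparison of one score, and it is also one of three repeated scores. If the ANOVA were used, neither of its treatment-related tests answers the 24 h question:

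- The group main effect averages over all times. Randomisation makes the expected difference at T_before zero, so that time pulls the average towards no effect.
- The group-by-time test asks whether the two profiles differ in shape anywhere. A difference at 72 h alone can make it significant.

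The same dilution applies to the three markers, MAP and HR through T0. At stake are which result decides the trial, and whether the secondary analyses, including the markers behind the mechanistic aim in section 2, report a difference at the times that matter.

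**Working it through.** **Inputs.** Section 3.7 gives 42 per group, 80% power, two-sided α 0.05 and an MCID of 8.0, taken here as the design difference because the text does not say so outright. The protocol gives neither an SD nor a correlation between times. The SD is back-solved. Correlations ρ of 0.3, 0.5 and 0.7, equal between all pairs of times, are assumed.

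**Step 1: what the sample size was built for.** A two-sample t-test with difference 8, 42 per arm and SD 12.9 has standard error 12.9 × √(2/42) = 2.82 and exact power 80.2%. At SD 13.0 the power is 79.6%. The stated 42 therefore fits a two-group comparison of a single 24 h score with SD about 12.9.

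**Step 2: group main effect over three times.** The tested difference is the mean of the three differences. The SD of a patient's three-time mean is 12.9 × √((1+2ρ)/3), which is 9.42, 10.53 and 11.54 at ρ = 0.3, 0.5 and 0.7. Multiplying by √(2/42) gives standard errors of 2.06, 2.30 and 2.52.

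**Step 3: group-by-time test.** The F test has 2 and 164 degrees of freedom. Its noncentrality is (42/2) × S / (12.9² × (1−ρ)), where S is the sum of squared deviations of the three differences from their mean. For (0, 8, 0), (0, 8, 8) and (0, 0, 8), S = 42.67 in every case. For (0, 8, 4), S = 32.

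| True difference (before, 24 h, 72 h) | Mean difference | Group effect, power at ρ 0.3 / 0.5 / 0.7 | Interaction, power at ρ 0.3 / 0.5 / 0.7 | 24 h t-test |
|---|---|---|---|---|
| 0, 8, 0 | 2.67 | 25 / 21 / 18% | 69 / 84 / 97% | 80% |
| 0, 8, 4 | 4.00 | 48 / 40 / 35% | 56 / 71 / 91% | 80% |
| 0, 8, 8 | 5.33 | 73 / 63 / 55% | 69 / 84 / 97% | 80% |
| 0, 0, 8 | 2.67 | 25 / 21 / 18% | 69 / 84 / 97% | 5% |

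The first, third and fourth rows have the same interaction power because S is the same. The interaction test cannot tell an effect at 24 h only from one at 72 h only or at both. Simulation with 20,000 trials per scenario at SD 13.0 agrees with these figures to within about two percentage points.

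**Step 4: type I error if the choice stayed open.** Simulated with no effect at any time, for ρ = 0.3 / 0.5 / 0.7: counting either the 24 h t-test or the group effect gives 8.6 / 7.7 / 7.2%. Counting any of the t-test, group effect or interaction gives 12.4 / 11.9 / 11.5%.

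**Step 5: using the pre-surgery score as a covariate.** ANCOVA at 24 h (simulated, SD 13.0, true difference 8) has power of about 83 / 89 / 97%, against about 80% for the unadjusted t-test.

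**The case against.** The best defence is that the primary target is not in doubt. Sections 3.4 and 3.7 both name QoR-15 at 24 h, the sample size fits a two-group comparison of that one score, and section 3.7 supplies a two-sample test for it. The natural reading is a two-sample test for the primary and ANOVA for the series, with further detail left to an analysis plan. Much of this stands, and it rules out several stronger readings that a reader might infer:

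- *The trial has only 18–25% power.* That requires the ANOVA main effect to decide the trial, which the protocol does not say. The t-test keeps about 80%, and the interaction has 56–97% in the scenarios with a 24 h effect.
- *The type I error is 12%.* That requires a rule under which any significant test counts. No such rule is stated.
- *Every repeated outcome is affected.* VAS and PCIA presses have no pre-treatment value.
- *The marker analyses are badly underpowered.* The protocol gives no effect size for the markers. A low figure also depends on assuming no effect at T1, although T1 follows the planned loading dose.
- *A missing 72 h score would delete an observed 24 h score.* Classical ANOVA does work that way, but section 3.2 already eliminates patients lost to follow-up, and no 72 h missingness rate is given to size the effect.

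Section 3.7 also does not list the times that enter the ANOVA, so including the pre-treatment value is the literal reading and not an explicit statement. What the defence does not remove is that the protocol itself states two methods that both cover its primary endpoint, without ranking them.

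**Conclusion.** The point holds as an ambiguity in the primary analysis and a poor choice of model for outcomes with a pre-treatment value. It should be fixed, but it does not show that the trial is underpowered or its error rate inflated as planned.

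If the ANOVA group effect were used for QoR-15, power for an 8-point effect at 24 h would be about 18–25%, 35–48% or 55–73%, according to whether none, half or all of it remains at 72 h. If the interaction were used, it would be significant in about 69–97% of trials with an effect at 72 h only, where the 24 h t-test stays at 5%. Leaving the choice open until the data are seen would put the type I error at about 7–9% (two tests) to 12% (three tests). All of this rests on the back-solved SD, 8.0 as the design difference, 42 evaluable patients per arm and the assumed equal correlations of 0.3 to 0.7.

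**What to change.** In section 3.7, state that the primary test is one between-group comparison of QoR-15 at 24 h by ANCOVA with the T_before score as covariate, and that any repeated-measures analysis of QoR-15 is secondary. Naming this one test also removes the choice between t-test and Mann-Whitney for the primary.

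For the other repeated outcomes, replace the ANOVA with a mixed model on post-treatment times, with group, time and group-by-time as terms and the pre-treatment value (T0) as covariate. VAS takes the same model without that covariate. Report the group difference with its 95% confidence interval at each named time.

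The cost is wording and slightly more analysis work. T_before and T0 are already in the measurement schedule, so no new data or patients are needed.

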**2. Objective and implication**

This study aims to observe the effect of low-dose esketamine on the early postoperative quality of recovery in patients undergoing laparoscopic radical resection of colorectal cancer and whether it can regulate the level of inflammation through NLRP3 inflammasome, reduce postoperative pain, and improve postoperative recovery of patients, so as to provide reference for the rational use of esketamine in total intravenous anesthesia.

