**4. Anticipated study results**

Low-dose esketamine can improve the early postoperative quality of recovery in patients undergoing laparoscopic radical resection of colon cancer. It can regulate the level of inflammation through NLRP3 inflammasome, reduce postoperative pain, improve postoperative recovery of patients, and provide reference for the rational use of esmketamine in total intravenous anesthesia in patients undergoing radical resection of colorectal cancer.

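### One two-sided P < 0.05 rule covers every outcome, while aims on inflammation, pain and recovery rest mainly on many unranked secondary outcomes

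*Protocol*

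**What the plan says.** Protocol section 3.4 names one primary endpoint: "The primary outcome of this study is quality of recovery at 24 h after surgery", measured by QoR-15. The same paragraph schedules QoR-15 before surgery and at 72 h. Six groups of secondary outcomes follow. They include three inflammatory markers at four times, and "VAS pain scores at rest (VAS-R) and on coughing (VAS-M) at 4h, 8h, 12h, 24h and 48h postoperatively".

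Section 2 sets further aims beside the effect on early quality of recovery, namely "whether it can regulate the level of inflammation through NLRP3 inflammasome, reduce postoperative pain, and improve postoperative recovery of patients". Section 4, on anticipated results, repeats them in the affirmative: "It can regulate the level of inflammation through NLRP3 inflammasome, reduce postoperative pain, improve postoperative recovery of patients".

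Section 3.7 sizes the trial on the primary outcome alone: the MCID "in the QoR-15 scale was 8.0", and "42 subjects in each group were required to achieve 80% power with an α of 0.05". It then lists Student's t-test, repeated measures ANOVA for data at several times, Mann-Whitney, and chi-square or Fisher tests. It closes with one rule for all of them: "A two-sided test" with P "less than 0.05 was considered statistically significant". No outcome is exempted, ranked or called exploratory.

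**The concern.** The rule and the aims do not fit together. With one primary endpoint and no further claims, a general 0.05 threshold would do little harm. Here, inflammation and pain are aims in their own right and are measured only by secondary outcomes. Recovery is measured partly by the primary endpoint and partly by several secondary ones. The protocol does not say which variable decides each aim. Under the stated rule, one nominally significant result among several could be read as meeting an aim.

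At stake is what the trial may report. A statement that esketamine lowers inflammation, reduces pain or speeds recovery could rest on the most favourable of many tests, with an error rate well above the 5% that the threshold suggests. The conclusion on QoR-15 at 24 h is not affected.

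**Working it through.** **The plan's own figure.** The protocol gives no family-wise error rate and no count of secondary tests, so there is none to reproduce. The 0.05 in the sample size belongs to the primary comparison. No SD is stated, so 42 per group cannot be derived from the stated inputs. It follows if the SD is about 13: n = 2 × [(1.960 + 0.842) × 13 / 8]² = 41.5, rounded up to 42. The calculation makes no provision for any other outcome.

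**Family of tests (an assumption).** I count one test per outcome behind the three aims, from section 3.4:

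- Inflammation, 3: NLRP3, IL-1β, IL-18.
- Pain, 6: VAS at rest, VAS on coughing, effective PCIA presses, oxycodone consumption, additional analgesics, rescue analgesia in the PACU.
- Recovery, 4: hospital stay, intestinal function recovery time, time to first eating or drinking, ambulation time.

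The total is 3 + 6 + 4 = 13. QoR-15 at 72 h is left out because it stands under the primary outcome heading. Repeated measurements count once, in keeping with the repeated measures ANOVA in section 3.7. Intraoperative variables, haemodynamics, emergence times and adverse events are left out because they do not bear directly on the three aims.

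**Either direction, independent tests, no true effects.** P(at least one P < 0.05) = 1 − 0.95^k.

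- k = 13: 1 − 0.95^13 = 1 − 0.513 = 0.49
- k = 3 (the markers alone): 1 − 0.857 = 0.14

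**Either direction, correlated tests.** The outcomes are surely correlated, but the protocol gives no values. I took standard normal test statistics with a common correlation ρ, each significant when |z| > 1.96:

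| Tests | ρ = 0 | ρ = 0.3 | ρ = 0.5 | ρ = 0.8 |
|---|---|---|---|---|
| 3 | 0.14 | 0.14 | 0.13 | 0.10 |
| 13 | 0.49 | 0.42 | 0.33 | 0.19 |

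**False benefit only.** A two-sided test at 0.05 has 0.025 in the direction that favours esketamine. With each outcome oriented so that benefit is positive, and z > 1.96 required:

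- independent: 1 − 0.975^13 = 1 − 0.720 = 0.28
- ρ = 0.5: 0.17
- ρ = 0.8: 0.10

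**Sensitivity to time points.** Section 3.7 sends non-normal data to the Mann-Whitney test and names no non-parametric method for repeated measurements. If that led to a separate comparison of each VAS score at each time, there would be 2 × 5 = 10 tests for VAS alone. The either-direction chance would then be 0.29 at ρ = 0.5 (0.17 at 0.8, 0.40 if independent). This is conditional and does not enter the main figure.

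**The case against.** **The absence of a multiplicity procedure is no finding.** Testing order, alpha allocation and exploratory labels are commonly left to an SAP, which is not shown, and many trials report nominal secondary P-values. This stands as far as it goes: silence alone would not be a point. But section 3.7 is not silent. It fixes one threshold for all the tests it lists, and section 2 attaches aims to the outcomes that they serve.

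**Section 4 draws no conclusions.** This stands. A reader might infer from its affirmative wording that the protocol already concludes that esketamine acts on inflammation and pain, or that any one significant secondary result proves a claim even if the primary fails. The heading announces anticipated results, section 2 asks whether the effects occur, and no sentence sets such a proof rule. What the documents support is narrower: the stated rule leaves that reading open.

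**No single error rate follows from the protocol.** This also stands. The figure depends on the chosen family and the assumed correlation. A reader might take about one in three as the risk of a false claim of benefit. It counts results in either direction, and the benefit-only figure is about half of it. Nor does it cover every secondary outcome, since the family is limited to those behind the three aims.

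**Recovery is partly a primary matter.** Correct: quality of recovery at 24 h is the primary endpoint. The point therefore applies in full to inflammation and pain, and only in part to recovery.

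**The trial's size does not inflate error.** Correct. A sample of 42 per group does not make false positives more likely, and nothing here rests on that.

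**Conclusion.** The point holds as a proportionate improvement, not as a flaw in the primary analysis. The primary test keeps its two-sided 5% error. For the secondary outcomes behind the inflammation, pain and recovery aims, the uniform 0.05 rule leaves the chance of at least one false-positive result well above 5%. It is about one in three in either direction and about one in six for false benefit, at the central correlation.

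These figures rest on three assumptions: 13 tests with one per outcome, equal correlations between 0 and 0.8, and no true effect on any of the outcomes. The ranges in the working show how far they move. For the 13-test family the conclusion does not depend on the exact correlation, because even at 0.8 both figures are nearly four times the per-test level (0.19 against 0.05, and 0.10 against 0.025).

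**What to change.** In section 3.7, state that QoR-15 at 24 h is the only confirmatory test, at two-sided 0.05. State that all other outcomes and time points, including QoR-15 at 72 h, are exploratory. They would be reported as between-group estimates with 95% confidence intervals and unadjusted P-values, which do not by themselves establish an effect.

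In section 4, reword the statements on inflammation, pain and other recovery effects as exploratory expectations.

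The cost is a few sentences. No patients or data are added, and the primary test loses no power. The downside is that isolated significant secondary results can no longer be stated as demonstrated effects. Formal testing of selected secondary outcomes in a fixed order would be a matter of preference and is not needed to settle this point.
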